#### *Adverse events*

Any complaints and symptoms, including pain, skin irritations, bruise at acupuncture points, subcutaneous bleeding, dizziness, and any other unusual responses will be monitored and recorded throughout the whole study period.

#### *Dropouts and withdrawals*

All dropouts and attrition during the course of the study will be monitored and recorded with respective reasons.

#### *Statistical issues*

##### *Sample size determination*

The sample size will be determined with a general acceptance of probability of 0.05 in committing a type I error and a power of 80%. For two arms (control — sham abdominal acupuncture and experimental — real abdominal acupuncture), repeated measures of analysis of variance (ANOVA) model will be used. An effect size of 0.2, which considered as small by Cohen [42], will be adopted. By using the power analysis program G\*Power 3 [43] with consideration of equal allocation between the two groups and a dropout rate of 15%, it is estimated that each group will require 77 subjects, with a total sample size of 154 subjects for this study.

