### *Statistical methods and analysis*

Analyses of data in this study will be performed by using statistical analysis software (SPSS 20.0). Two-sided significance will be defined as  $P < 0.05$ .

All the demographic, clinical, baseline and adverse events data will be analyzed descriptively, using means and standard deviations and 95% confidence intervals (CIs) for the continuous variables and percentages for the categorized ones. These data will be performed separately for each study group. Baseline characteristics of all study groups will be compared to examine homogeneity. Independent two-sample t-test will be used to determine possible baseline differences for quantitative data. The Chi-square test will be used to determine possible differences for qualitative data.

An intention-to-treat approach will be used for all analyses in this study for all the randomized patients to assess the efficacy of abdominal acupuncture treatment. Missing data will be replaced with the last value obtained from the patients, and such value will be carried forward if no additional value obtained. This approach is based on the assumption that patients who have missing values do not have improvement since the last follow-up assessment and may expect no further benefit from the therapy.

Repeated measures ANOVA will be used as single overall tests for the effects of treatment and for the comparison between real and sham abdominal acupuncture groups at baseline, immediately after the intervention ends, and at 4-week follow-up interviews. The ANOVA will be performed for each outcome variable separately. Between groups effects of measurement for each outcome variable at different assessments will be analyzed by ANOVA while the difference of outcomes between

real and sham abdominal acupuncture groups will be assessed by the independent sample t-test.

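### The protocol claims 80% power for a small effect of 0.2 without naming the metric; 77 per arm fits Cohen's f = 0.2, and a standardised difference of 0.2 would have about 20–33% power

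*Protocol*

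**What the plan says.** The Sample size determination section sets a "general acceptance of probability of 0.05 in committing a type I error" and 80% power, and says that a "repeated measures of analysis of variance (ANOVA) model will be used" for the two arms. On the effect, it says: "An effect size of 0.2, which considered as small by Cohen [42], will be adopted". With G\*Power 3, 1:1 allocation and 15% dropout, "it is estimated that each group will require 77 subjects, with a total sample size of 154 subjects for this study".

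The section does not say which effect-size metric 0.2 refers to. It gives no number of repeated measurements, no correlation between them, and no difference or SD in points of the Northwick Park questionnaire.

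The Statistical methods and analysis section makes testing two-sided and plans the repeated-measures ANOVA on measurements "at baseline, immediately after the intervention ends, and at 4-week follow-up interviews", so three time points with baseline among them. It assigns the direct comparison of the arms to an independent-sample t-test. The Outcome measurements section puts the primary endpoint at the end of the intervention.

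**The concern.** By the usual convention, 0.2 is the small benchmark for a standardised mean difference d, while the small benchmark for f is 0.1. G\*Power's repeated-measures ANOVA routines take f. For two equal groups f = d/2, so the same number entered as f describes an effect twice as large as when it is read as d. A reader who takes the sentence at face value will believe that the trial can detect 0.2 SD with 80% power.

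If the sample size rests on f = 0.2, that belief is wrong by a wide margin. The power statement would then mislead anyone who uses it to judge what a null result says about small benefits.

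**Working it through.** **Inputs from the protocol:** two-sided alpha 0.05, power 80%, two equal arms, effect size 0.2, dropout 15%, 77 per arm. Three measurements (m = 3) come from the analysis section. **Assumed:** the correlation rho between measurements, which the protocol does not give; 0.5 is used, with 0.3 to 0.7 as a range.

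**1. Reproducing 77 per arm with 0.2 as f.** For the between-groups effect in a repeated-measures ANOVA, the noncentrality is lambda = N f² m / [1 + (m − 1) rho], with 1 and N − 2 degrees of freedom.

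- m = 3, rho = 0.5: lambda = 134 × 0.04 × 3 / 2 = 8.04, power 80.4%. N = 134 is the smallest even total reaching 80%, and 134 × 1.15 = 154.1, or 77 per arm.
- m = 2, rho = 0.3: lambda = 130 × 0.04 × 2 / 1.3 = 8.00, power just above 80%. N = 130, and 130 / 0.85 = 152.9, again 77 per arm after rounding up.

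Both routes use f = 0.2. The protocol does not show which was taken, if either.

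**2. Trying 0.2 as d.**

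- Same model, f = 0.1, m = 3, rho = 0.5: lambda = 526 × 0.01 × 3 / 2 = 7.89, so 526 completers in total (263 per arm).
- Two-sample t-test, d = 0.2: 394 per arm.

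Neither is near 77.

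**3. What f = 0.2 means as a difference.** d = 2f = 0.4 SD, averaged over the visits in the model. Randomisation makes the expected baseline difference zero. With baseline as one of three visits, the average is (0 + x + x)/3 = 0.4, so x = 0.6 SD at each follow-up visit. If the follow-up difference were 0.4 SD, the average would be 0.267 SD (f = 0.133), and power would be 46% (N = 130) to 52% (N = 154).

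**4. Power at a standardised difference of 0.2.** Both 154 patients and the 130 left after 15% loss (154 × 0.85 = 130.9) are shown.

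| Test | 130 patients | 154 patients |
|---|---|---|
| Independent t-test at one time point | 20.5% | 23.4% |
| ANOVA between groups, m = 3, rho = 0.5, average difference 0.2 SD | 28.3% | 32.7% |
| Same ANOVA, 0.2 SD at follow-up and zero at baseline | 15.2% | 17.2% |

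Moving rho from 0.3 to 0.7 shifts the second row to between 24% and 39%.

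**5. Detectable difference at the primary time point.** For the t-test with 80% power, the approximation is d = (1.960 + 0.842) × √(2/n). With n = 77 this is 2.802 × 0.161 = 0.45 SD. With n = 65 it is 2.802 × 0.175 = 0.49 SD. The exact noncentral-t values are 0.454 and 0.495, so about 0.45 to 0.50 SD.

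**The case against.** The strongest reply is that the arithmetic is not wrong. The protocol never says d. It names a repeated-measures ANOVA, whose effect size in the named software is f, and f = 0.2 does lead to about the stated number. This stands, so the defect lies in the unnamed metric and the label, and the 20–33% applies only to someone who reads 0.2 as a standardised difference. The label invites that reading.

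The label's meaning rests on convention, since the cited textbook is not at hand. The conversion d = 2f and the power figures do not depend on it.

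One route to 77 per arm uses f = 0.1: a group-by-time interaction with three visits and rho = 0.6 needs 130, and 130 / 0.85 gives 77 per arm. It requires entering 0.1 where the protocol says 0.2. It does not rescue a 0.2 SD claim either. With zero difference at baseline and x at both follow-ups, the interaction f is (x/2) × √(2/9), so f = 0.1 means x = 0.2 / 0.471 = 0.42 SD.

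A reader might also infer three stronger points, which the protocol does not support:

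- *The sponsor must have used three visits and a correlation of 0.5.* The two-measurement route fits equally well.
- *Dropout was inflated wrongly, as 67 × 1.15 = 77 instead of 67 / 0.85 = 79.* That follows only on the three-visit route. On the two-measurement route the inflation is correct. At most it costs under one point of power (79.2% with 130 completers, against 80%).
- *The trial will be analysed on 130 completers.* The plan is intention-to-treat with last values carried forward, so the analysed number is 154. At f = 0.2 the three-visit model then gives 85.6%, before any dilution from carried-forward values.

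Nor does the protocol say that a null result would exclude a small benefit. Its Conclusion presents the trial as groundwork for a later full-scale study.

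**Conclusion.** The point holds as a misstatement of what the sample size can detect. The 77 per arm is consistent with f = 0.2 and not with a standardised difference of 0.2, for which the same ANOVA model needs about 3.4 times as many patients (526 against 154). The power shortfall at that difference is large under every variant above.

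The ANOVA figures assume three visits and a correlation of 0.5; the t-test figures need neither. The identification of f is an inference from the numbers, since the protocol does not name it.

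A reader might conclude that 154 is too few and the trial must be enlarged. The protocol does not support that, because it gives no smallest important difference in questionnaire points against which 154 could be called inadequate. What needs correcting is the statement of effect size and power.

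**What to change.** Keep 154 patients and rewrite the sample size paragraph:

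1. Name the effect-size metric, the routine, the number of measurements and the correlation, taken from the sponsor's own calculation record. The values used in this check are back-calculated and should not be adopted as the sponsor's inputs.
2. If f was entered, delete the description of the effect as small. Say what f = 0.2 means: 0.4 SD averaged over the visits in the model, and about 0.6 SD at each follow-up visit if baseline is one of three.
3. State the detectable difference at the end of intervention for the planned comparison: for 80% power by the independent t-test, about 0.45 SD with 154 analysed and 0.50 SD with 130 completers. Translate it into questionnaire points if an SD is available.

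This is a wording change with no effect on recruitment, design or analysis. Its only cost is a less favourable power statement. If the sponsor did intend 0.2 SD, the 80% claim cannot stand at 154: by t-test it would take 394 per arm before dropout, or 394 / 0.85 = 464 per arm randomised.

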### *Statistical methods and analysis*

Analyses of data in this study will be performed by using statistical analysis software (SPSS 20.0). Two-sided significance will be defined as  $P < 0.05$ .

All the demographic, clinical, baseline and adverse events data will be analyzed descriptively, using means and standard deviations and 95% confidence intervals (CIs) for the continuous variables and percentages for the categorized ones. These data will be performed separately for each study group. Baseline characteristics of all study groups will be compared to examine homogeneity. Independent two-sample t-test will be used to determine possible baseline differences for quantitative data. The Chi-square test will be used to determine possible differences for qualitative data.

An intention-to-treat approach will be used for all analyses in this study for all the randomized patients to assess the efficacy of abdominal acupuncture treatment. Missing data will be replaced with the last value obtained from the patients, and such value will be carried forward if no additional value obtained. This approach is based on the assumption that patients who have missing values do not have improvement since the last follow-up assessment and may expect no further benefit from the therapy.

Repeated measures ANOVA will be used as single overall tests for the effects of treatment and for the comparison between real and sham abdominal acupuncture groups at baseline, immediately after the intervention ends, and at 4-week follow-up interviews. The ANOVA will be performed for each outcome variable separately. Between groups effects of measurement for each outcome variable at different assessments will be analyzed by ANOVA while the difference of outcomes between

real and sham abdominal acupuncture groups will be assessed by the independent sample t-test.

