### ***Outcome measurements***

#### ***Baseline information***

Sociodemographic information of all participants, including age, gender, education background and neck pain history including pain sites (unilateral neck, bilateral neck, central neck), pain duration, pain occurrence, previous neck injury, and previous neck treatments, will be recorded at baseline interview. An outcome assessor who is masked to treatment allocation will conduct assessments.

The study's primary endpoint will be immediately after the intervention ends. Table 1 below summarizes the categories of information and measurements that are included in the baseline and follow-up interviews.

Table 1. Content of baseline and follow-up assessments

| Measures                                   | Baseline | Finished | 4-week | 12-week |
|--------------------------------------------|----------|----------|--------|---------|
| Inclusion and exclusion variables          | X        |          |        |         |
| Sociodemographic characteristics           | X        |          |        |         |
| Neck pain history                          | X        |          |        |         |
| Neck Pain Questionnaire - Real             | X        | X        | X      | X       |
| - Sham                                     | X        | X        | X      |         |
| VAS for pain intensity † - Real | X        | X        | X      | X       |
| - Sham                                     | X        | X        | X      |         |
| SF-36v2 Health Survey - Real               | X        | X        | X      | X       |
| - Sham                                     | X        | X        | X      |         |
| Credibility test                           | X        | X        |        |         |
| Satisfaction with treatment                |          | X        |        |         |
| Blinding assessment †           |          | X        |        |         |
| Use of medications *            | X        | X        | X      | X       |
| Adverse experiences *           |          | X        | X      | X       |
| Dropouts and withdrawals *      | X        | X        | X      | X       |

\* At every single visit; † After the first treatment

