### *Primary outcome measure*

The primary outcome measure is the Northwick Park Neck Pain Questionnaire (NPQ) [29]. It is a questionnaire used to evaluate functional performance in patients with neck pain [5]. In this study, the validated Chinese version of the NPQ will be used [30-32]. It consists of nine five-part questions to assess the patient's symptoms and a score is obtained [29]. The questions cover activities which are likely to be affected

by neck pain. Each question contains five statements of increasing difficulty and is scored between 0 to 4. The NPQ will be scored out of 36, or 32 for non-car drivers, and is presented as a percentage [29,33]. In this study, the questionnaire will be assessed at baseline, immediately after the intervention ends, at 4-week, and 12-week follow-up interviews for real abdominal acupuncture group. As for sham abdominal acupuncture group, the questionnaire will be assessed at baseline, immediately after the intervention ends, and at 4-week follow-up interview.

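### Last value carried forward is the only stated missing-data rule, and at the primary endpoint it scores every patient without an end-of-treatment NPQ as unchanged from baseline

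*Protocol*

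**What the plan says.** All of this is in the Protocol.

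- **Rule** (Statistical methods and analysis): "Missing data will be replaced with the last value obtained from the patients", and that value is kept for later visits until a new one is recorded.
- **Scope** (same section): "An intention-to-treat approach will be used for all analyses in this study for all the randomized patients".
- **Rationale** (same section): the rule rests on assuming that "patients who have missing values do not have improvement since the last follow-up assessment and may expect no further benefit from the therapy".
- **Primary time point** (Baseline information): "The study's primary endpoint will be immediately after the intervention ends".
- **NPQ schedule** (Primary outcome measure and Table 1): baseline, end of intervention and 4 weeks in both arms, plus 12 weeks in the real arm. No NPQ falls between baseline and the primary endpoint. The VAS differs, because it is also taken after the first treatment.
- **Dropout** (Sample size determination): 15%, with 77 patients per group and 154 in total.

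The Protocol states no other way of handling missing outcomes.

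**The concern.** For the primary outcome, carrying the last value forward to the primary endpoint means carrying the baseline forward. This applies even to a patient who misses the end-of-treatment visit and returns at 4 weeks.

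The rule gives the right mean only if patients with missing values truly did not improve from before treatment. That is doubtful in both arms. Entry requires a VAS of 3 or more at screening, which invites regression to the mean. No minimum pain duration is set, so some natural recovery is plausible. Both arms also lie under an infrared lamp for 30 minutes per session.

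If patients do improve, the rule pulls each arm's mean back toward baseline in proportion to the share missing in that arm. The size, and with unequal dropout the direction, of the error in the primary comparison then depends on who happens to leave.

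**Working it through.** **1. The plan's own figure.** The stated 154 can be reproduced as a between-groups repeated-measures ANOVA with λ = f²·N·m / (1 + (m − 1)ρ). The inputs are f = 0.2, m = 3 visits, two-sided α = 0.05, power 80% and ρ = 0.5 (ρ is assumed; the Protocol gives none). This yields N = 134, or 67 per group, and 67 × 1.15 = 77.05, so 77 per group. For two groups f = 0.2 corresponds to d = 0.40, which is the true difference used below.

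**2. How many outcomes could be affected.** 0.15 × 154 = 23.1, so at most about 23 primary outcomes would be copied baselines under the planned rate. The Protocol does not say how much of the 15% falls before the end of treatment.

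**3. Bias.** Let p be the proportion missing at the primary endpoint and i the mean improvement in SD units, with R for real and S for sham. Under random dropout:

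- Expected estimate = (1 − p_R)·i_R − (1 − p_S)·i_S
- True difference = i_R − i_S
- Bias = p_S·i_S − p_R·i_R

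Sham improvement and the split of dropout between arms are assumptions.

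| Missing, real / sham | i_R | i_S | True | Carry-forward estimate |
|---|---|---|---|---|
| 15% / 15% | 1.2 | 0.8 | 0.40 | 1.02 − 0.68 = 0.34 |
| 5% / 5% | 1.2 | 0.8 | 0.40 | 1.14 − 0.76 = 0.38 |
| 20% / 10% | 1.2 | 0.8 | 0.40 | 0.96 − 0.72 = 0.24 |
| 10% / 20% | 1.2 | 0.8 | 0.40 | 1.08 − 0.64 = 0.44 |
| 15% / 15% | 0.8 | 0.8 | 0 | 0.68 − 0.68 = 0 |
| 10% / 20% | 0.8 | 0.8 | 0 | 0.72 − 0.64 = 0.08 |
| 5% / 25% | 0.8 | 0.8 | 0 | 0.76 − 0.60 = 0.16 |

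**4. Power, like for like.** Simulation with 77 per arm, baseline–outcome correlation 0.5, random dropout, true difference 0.40, sham improvement 0.8 SD and 20,000 trials per scenario:

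| Missing per arm | Analysis | Observed values | Carry-forward |
|---|---|---|---|
| 15% | t-test on end score | 62% | 51% |
| 15% | ANCOVA on baseline | about 75% | 65% |
| 5% | t-test on end score | 67% | 63% |

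**5. Type I error of the t-test under carry-forward** (same set-up, no true effect):

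| Missing, real / sham | Improvement in both arms | Type I error |
|---|---|---|
| 15% / 15% | 0.8 SD | 5% |
| 13% / 17% | 0.8 SD | 5–6% |
| 10% / 20% | 0.3 SD | about 5% |
| 10% / 20% | 0.5 SD | about 6% |
| 10% / 20% | 0.8 SD | 7.6% |
| 5% / 25% | 0.8 SD | about 16% |

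The same tests on observed values stay at about 5% throughout. Adding baseline adjustment while keeping carry-forward does not remove the inflation (about 9% at 10% / 20% and 0.8 SD), so the imputation is the cause.

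**The case against.** The strongest reply is that the effect may be small. Treatment lasts two weeks, while dropout is tracked to 12 weeks. A patient lost after the end of treatment has an observed primary NPQ that the rule never touches. Dropout may also be balanced, and then there is no false-positive problem. All of this stands, and it limits the size of the point. It does not rescue the rule, which acts on whatever is missing at the primary endpoint. Nor can the matter be left to a statistical analysis plan, because the Protocol itself fixes the rule, its scope and its rationale.

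Four stronger readings are tempting but unsupported:

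- **Carry-forward costs more than 20 points of power.** A reader might compare the unadjusted carry-forward t-test (51%) with a baseline-adjusted analysis of observed values (about 75%). That changes two things at once. Like for like, the loss is about 10 points.
- **The trial's type I error is inflated.** This needs unequal dropout together with sizeable improvement in both arms. The Protocol gives neither, and the 16% figure needs a fivefold imbalance.
- **The standard errors are wrong because imputed values count as real.** In simulation (change scores, 15% missing per arm, 0.5 SD sham improvement) the model standard error under carry-forward was 0.154, equal to its sampling standard error. The harm is bias.
- **An observed-data analysis is shown to be valid when patients leave because treatment fails.** The simulations use random dropout, so they say nothing about that case.

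The opposite inference, that the rule is safely conservative, also fails: with 10% missing in the real arm and 20% in sham, it favours real treatment in the null case above.

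**Conclusion.** The point holds and should be fixed. The rule replaces a missing primary outcome with a pre-treatment value, on an assumption that the trial's own entry criteria and shared lamp treatment make doubtful.

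With equal dropout the consequence is dilution: 15% of the effect at most under the planned rate (0.40 to 0.34), and proportionally less if fewer patients are lost before the end of treatment. With unequal dropout the bias can go either way. Type I error is then close to nominal for mild imbalance or small improvement, and clearly inflated only in the more extreme assumed scenarios.

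These figures rest on an assumed correlation of 0.5, assumed improvements of 0.3 to 0.8 SD, random dropout and assumed arm splits. The zero-change scoring itself needs none of them, since it follows directly from the rule and the visit schedule.

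**What to change.** In Statistical methods and analysis, delete the carry-forward sentence and its no-improvement rationale. In their place specify a likelihood-based mixed model on the observed NPQ values with treatment, visit and treatment-by-visit, reporting the end-of-treatment contrast as primary. Enter baseline NPQ as one of the repeated responses, so that randomised patients with no post-baseline value stay in the model and the intention-to-treat set is kept. Multiple imputation is an acceptable alternative. Keep carry-forward as a sensitivity analysis.

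The cost is a paragraph of wording and a little programming with the MIXED procedure of the SPSS software already named. No visit, procedure or patient number changes. It should be settled before unblinding. The downside is that the primary result then relies on data being missing at random. One sensitivity analysis that departs from that assumption can probe it, and its details can sit in the statistical analysis plan.

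### No test of NPQ at end of treatment is fixed as primary: the overall ANOVA counts baseline as an outcome visit, which dilutes its group main effect, and the endpoint t-test names no baseline adjustment

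*Protocol*

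**What the plan says.** Under Outcome measurements (Baseline information), the protocol fixes the time: "The study's primary endpoint will be immediately after the intervention ends". Primary outcome measure names the NPQ and has it collected at baseline in both arms.

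Statistical methods and analysis says "Repeated measures ANOVA will be used as single overall tests for the effects of treatment", comparing the arms at baseline, end of intervention and 4 weeks. It then plans ANOVA of between-group effects at the different assessments, and says that the difference of outcomes between "real and sham abdominal acupuncture groups will be assessed by the independent sample t-test". It does not say which ANOVA term is the treatment test, which of these tests decides the primary endpoint, or whether the t-test uses raw or change scores. It names no baseline covariate.

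Sample size determination says that a "repeated measures of analysis of variance (ANOVA) model will be used", with "general acceptance of probability of 0.05 in committing a type I error and a power of 80" per cent. On the effect it says: "An effect size of 0.2, which considered as small by Cohen [42], will be adopted". The result is 77 per arm, 154 in total.

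**The concern.** The declared endpoint is one between-arm comparison at one visit. The test described as the overall test of treatment spans three visits, and one of them precedes treatment. If its group main effect is read as the treatment test, a visit with zero expected difference is averaged in with the visits that carry the effect. The comparison that does sit at the endpoint, the t-test, makes no stated use of a baseline score that is already collected and would sharpen it.

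The stakes are power and clarity, not bias. Each planned test is valid under randomisation. But a real effect of the planned size could be missed more often than the stated 80% power suggests, and the protocol does not say which NPQ result settles the question.

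**Working it through.** **Inputs from the protocol.** Alpha 0.05, two-sided ("Two-sided significance will be defined as" P < 0.05); power 80%; effect size 0.2; equal arms and 15% dropout ("with consideration of equal allocation between the two groups and a dropout rate of 15" per cent); 77 per arm. Completers: 77 × 0.85 = 65.45, taken as 65 per arm.

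**Assumptions, not stated in the protocol.** The effect size 0.2 is Cohen's f, so d = 2f = 0.4 for two equal groups. The SD is the same at every visit, with a common correlation ρ between visits: 0.5 as base case, range 0.3 to 0.7. The arm differences are 0 at baseline, 0.4 at end of treatment and 0.4 at 4 weeks.

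**1. Reproducing 154.** For a G*Power between-factors test with m visits, λ = f²·N·m / (1 + (m − 1)ρ). With f = 0.2, m = 3 and ρ = 0.5, λ = 0.04 × 3N / 2 = 0.06N. N = 134 gives λ = 8.04 and power 80.4%; N = 132 gives 79.8%. Then 134 × 1.15 = 154.1, which is the stated figure. Dividing instead gives 134 / 0.85 = 157.6.

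Two other input sets also give it:
- Between factors, m = 2, ρ = 0.3, f = 0.2: λ = 0.04 × 130 × 2 / 1.3 = 8.0, power 80.2% at N = 130.
- Interaction, m = 3, ρ = 0.6, f = 0.1: λ = 0.01 × 130 × 3 / 0.4 = 9.75, power 80.0% at N = 130.

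For both, 130 / 0.85 = 152.9, or 77 per arm after rounding up. The protocol does not say which route was used. The first one presumes the full difference at all three visits, baseline included.

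**2. Group main effect over three visits.** Mean difference (0 + 0.4 + 0.4) / 3 = 0.267, two thirds of 0.4. SD of a three-visit mean √((1 + 2ρ)/3) = 0.816. Effective d = 0.267 / 0.816 = 0.327. λ = (n/2) × 0.327² = 3.47 (n = 65) or 4.11 (n = 77).

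**3. Unadjusted t-test at end of treatment.** λ = (n/2) × 0.4² = 5.20 or 6.16, whatever ρ is.

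**4. Group-by-visit interaction.** The squared deviations of (0, 0.4, 0.4) from their mean sum to 0.267² + 2 × 0.133² = 0.1067. λ = (n/2) × 0.1067 / (1 − ρ) = 6.93 or 8.21, with 2 numerator df.

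**5. ANCOVA at end of treatment.** λ = (n/2) × 0.4² / (1 − ρ²) = 6.93 or 8.21, with 1 numerator df.

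| Test (ρ = 0.5) | 65 per arm | 77 per arm |
|---|---|---|
| Main effect, if 0.4 held at all three visits | 79.2% | 85.6% |
| Main effect, baseline difference 0 | 45.5% | 52.1% |
| Unadjusted endpoint t-test | 61.9% | 69.4% |
| Group-by-visit interaction | 64.5% | 72.5% |
| Baseline-adjusted ANCOVA at endpoint | 74.3% | 81.3% |

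**6. Sensitivity to ρ, 65 per arm.**

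| Test | ρ = 0.3 | ρ = 0.5 | ρ = 0.7 |
|---|---|---|---|
| Main effect | 54.2% | 45.5% | 39.3% |
| t-test, raw score | 61.9% | 61.9% | 61.9% |
| t-test, change score | 48.1% | 61.9% | 83.2% |
| Interaction | 49.5% | 64.5% | 86.6% |
| ANCOVA | 66.0% | 74.3% | 88.7% |

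If the 4-week effect is halved, the main effect has 28.3% power at ρ = 0.5; if it has gone, 15.2%. The end-of-treatment tests do not change.

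**7. Last value carried forward.** The 77-per-arm column treats every filled value as carrying the full effect. A value carried from baseline carries none. In a simulation of 8,000 trials (77 per arm, ρ = 0.5), 15% dropped out before any post-treatment visit. Power was about 39% (main effect), 56% (raw t-test) and 65% (interaction).

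**The case against.** The strongest reply has four parts.

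- **The t-test reaches the endpoint.** This stands. A reader might infer that none of the planned tests addresses the declared endpoint. The documents do not support that, because the by-visit ANOVA and the t-test can be applied to NPQ at end of treatment. With two arms at one visit they are the same test.
- **The interaction is not diluted as the main effect is.** This stands. It has 65% or 73% power at ρ = 0.5 and 87% or 92% at ρ = 0.7. But the protocol does not designate it, and it is a joint test over three visits, not the end-of-treatment difference. ANCOVA has more power than it at each ρ from 0.3 to 0.7. At ρ = 0.8 the two are level (97% each, 65 per arm).
- **The t-test might use change scores.** This is possible, since the text does not say. A change score does worse than the raw score at ρ = 0.3, equals it at 0.5 and beats it at 0.7. ANCOVA beats both throughout that range.
- **Term-level detail may sit in a statistical analysis plan that is not shown.** This is fair for detail. Here, however, the protocol itself names specific tests, and those tests fit its endpoint less well than one it could have named.

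Two further stronger readings fail. One is that the 80% must belong to a contrast that cannot occur; other input sets also give 77 per arm, so this is not shown. The other is that any significant NPQ test would count as success. The protocol declares one primary outcome and one time, and the t-tests can be read as follow-ups to the overall test.

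**Conclusion.** The point holds in this form: the declared endpoint has no test fixed as primary, the group main effect of the overall ANOVA is diluted to two thirds of a constant post-treatment effect, and the test available at the endpoint names no baseline adjustment. Under the base assumptions, moving to baseline-adjusted ANCOVA at 65 per arm raises power from 46% (main effect), 62% (t-test) or 65% (interaction) to 74%.

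Every percentage depends on ρ, on reading 0.2 as f, and on an effect that stays constant after treatment; Sample size determination states none of these. No single power figure can therefore be quoted as the trial's true power. If 0.2 was meant as d, the endpoint t-test has only about 20% to 23% power, so the scale must be stated. The dilution itself does not depend on ρ: it follows from randomisation and from including baseline as a visit.

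**What to change.** In Statistical methods and analysis, name one primary test: the between-arm difference in NPQ immediately after treatment, adjusted for baseline NPQ. Use ANCOVA, or a mixed model with baseline as covariate and the end-of-treatment and 4-week values as outcomes, reading the end-of-treatment contrast. Make the 4-week comparison and the other outcomes secondary, and analyse them in the same way.

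In Sample size determination, restate power for this test, giving the effect-size scale and the correlation. For example: about 74% at d = 0.4, ρ = 0.5 and 65 completers per arm, or 80% at d of about 0.43. The trial need not be enlarged.

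The cost is wording. Baseline NPQ is already collected, and the planned software fits both models. The downside is that the stated power becomes slightly less favourable than 80% at d = 0.4.
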